### Statistical analysis

We will compare results between the two years (with and without POC testing) from within the 150 patients aged 16–29 tested each year in participating health services. Characteristics of participating health services will be summarized at baseline and across trial arms (standard practice or POC phase). The primary endpoint of the study will be the health service specific difference between the two years in repeat positivity rates at three months. The secondary endpoint will be the health service specific difference between the two years in the proportion of true CT and NG infections that were treated within seven days of presentation. For both the primary and secondary endpoints, the average difference between the two years (with and without POC tests) will be calculated across participating health services. Other secondary outcomes will be measured as follows:

*Cultural acceptability of POC tests to patients*: will be assessed by a descriptive analysis of questionnaire feedback received from patients.

*Operational acceptability of POC tests to health service staff in remote community settings*: will be assessed by calculating the proportion of staff who indicated that they agreed or strongly agreed on the Likert scale with the acceptability questions in the staff questionnaire.

*The cost effectiveness of the addition of POC testing to standard diagnostic procedures*: The treatment interval, repeat positivity rate and contact tracing data collected in this trial will enable us to parameterise the models. Our analyses will apply similar techniques to those used by other studies in the context of POC tests [51,52], but explicitly represent regional and remote Australian Aboriginal community settings. Our approach will extend previous work by developing a more realistic model based on simulated sexual networks rather than population averages. The mathematical approach will use an individual-based model to enable us to accurately simulate and track repeat positivity rates, which is not possible with previous models. The epidemiological transmission models will project the estimated prevalence, incidence and repeat positivity rates expected from implementing POC tests in communities.

These model outputs will become inputs in a health economics analysis. The cost of using POC tests in regional and remote health services including the increased clinician and patient waiting time for POC tests and the patient costs incurred in a return visit to the health service for medication after a positive test result will be directly measured in the trial. These data will be used to estimate the additional cost of implementing POC tests in combination with NAAT testing, compared to standard diagnostic procedures. Costs related to research will be excluded.

The total costs associated with the widespread implementation of POC tests, including estimated logistical, clinical and administrative costs, will be compared with the long-term health and financial savings associated with their use (including the prevention of new infections, co-morbidities, and saving in reduced quality of life as well as costs of treatment saved due to decreased infections). As is standard with health economic analyses, discounting will be applied at levels of 0%, 3% and 5%. The health economic analyses will be carried out from the perspectives of the provider and the client. The integrated epidemiological and economic modelling will examine issues of allocation, efficiency, and cost-effectiveness.

*The sensitivity, specificity, negative and positive predictive value of the POC test in a field setting compared to the reference laboratory test*: POC test performance will be assessed by comparing the results of the POC tests performed during the POC phase with the reference test (NAAT).

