## Methods

### Study design

TTANGO is a crossover cluster randomised controlled trial set in 12 health services in regional or remote areas of Queensland, West Australia and South Australia (Figure 1: Study overview). Participating health services will undertake the clinical management of CT and NG under two different parallel modalities for one year each, in a randomly assigned order. In the first year, six of the health services will be randomly assigned to manage these infections under current diagnostic guidelines (“standard practice” phase or “control” phase). The other six will supplement current diagnostic guidelines with POC testing (“POC” phase), such that diagnosis is made and subsequent treatment for those with positive POC tests is offered at the time of initial consultation. In the second year, the health services will cross over to the opposite management modality. The study will require four years to complete, including 1.5 years preparation and community consultation, 2 years for the intervention and evaluation, and 6 months for analysis and reporting. The fundamental premise of the trial is that more timely treatment for STIs (both index case and partners), will result in a substantial reduction in the percentage of people with repeat positive CT and NG infections.

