### Randomisation

Health services within the four geographic regions will be randomised to intervention (“POC” phase) or control arm (“standard practice” phase) strategies for year one in a 1:1 ratio, and will cross over to the opposite arm in year two. Randomisation within geographic regions is mainly for pragmatic reasons so that the TTANGO coordinators are able to manage workload appropriately, and avoid the possibility of all services in one region being randomised to the same study arm. The randomisation scheme will be developed by the TTANGO statistician using SAS statistical software (Version 9.3) and will be communicated to participating health services once participation agreements have been signed.

During the ***POC Phase*** health services will continue routine STI testing and management practices (syndromic management, and sending off specimens to laboratories for routine NAAT tests) but will supplement their activity with CT and NG POC testing, so treatment and management of positive CT and NG POC tests occurs at the time of initial consultation. The POC test selected for the trial is the GeneXpert CT/NG® (Cepheid) which is a new test based on nucleic acid amplification technology, with dual detection of CT and NG in under 90 minutes. The GeneXpert CT/NG POC test had been demonstrated in laboratory and field evaluations in Australia [42,43] and the US [44] to have similar sensitivity and specificity to routine laboratory based NAAT tests, and was easy to use. The test has 5 targets, including a specimen processing control, specimen adequacy control, one CT target and two targets for NG. Two separate targets for NG allows for more specific detection and confirmation of NG [45]. The GeneXpert CT/NG test was approved by the Therapeutic Goods Administration for diagnostic purposes in Australia in March 2013, and obtained Conformité Européenne (CE) marking and US Food and Drugs Administration (FDA) clearance in 2012.

During the ***Standard Practice phase*** health services will maintain routine STI testing and management practices involving syndromic management, and sending off specimens to laboratories for routine NAAT tests, with treatment and management of asymptomatic infections based on the results that are received from the laboratory. The NAAT tests commonly used at the laboratories are the Roche Cobas and the Gen Probe Aptima.

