#### STI quality improvement

In both trial phases, de-identified clinical and laboratory data will be used to generate regular site specific reports on STI screening and management. Reports will show the percentage of health centre attendees patients tested for STIs, the percentage testing positive, time to treatment, the percentage re-tested 3 months after treatment, and the percentage with a repeat positive result at re-test. The reports will be discussed at initial and subsequent visits, and are intended to assist services to reflect on current practice and develop strategies to achieve best practice in STI service delivery [16,46,47]. Accordingly, health services will be supported to increase and appropriately target opportunistic STI testing, provide treatment promptly where indicated, and follow recommended guidelines for re-testing and contact tracing. Where necessary, TTANGO coordinators will respond to identified training needs to strengthen sexual health service delivery.

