### Sample size

Power calculations were performed using the methods of Julious et al. [49], for paired binary comparisons and Hayes et al. [50] for community randomised trials. We assumed that the prevalence of CT and/or NG will be 15% at recruitment to the trial in each year, that 30% of patients will have a positive re-test within three months (in the standard practice phase), and that at least 150 patients aged 16–29 years will be tested at each health service in both POC and standard practice years. Table 2 shows the total number of health services needed to detect a reduction in CT and NG repeat positivity rate from 30% in control health services to 15% in intervention health services with 80% and 90% power, differing community coefficients of variation (0.25, 0.30) and equal numbers of health services in each arm. At least ten services will provide data in both the intervention and control arms. This will ensure 88% power to detect a decrease in CT and NG repeat positivity rate from 30% to 15%, and 78% power to detect a reduction from 20% to 10%. Conservatively, 12 services will be included in the trial.

**Table 2 T2:** Sample size estimates based on reduction in repeat positivity rate from 30% to 15%

**Coefficient of variation**	**Number of services**	
	**80% power**	**90% power**
25%	8	10
30%	10	14

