## Discussion

Rates of CT and NG in remote Aboriginal communities in Australia are unacceptably high, and TTANGO will evaluate whether POC testing for these STIs can improve the timeliness of treatment and in turn reduce repeat infection rates. To our knowledge, TTANGO will be the first randomized trial of molecular POC tests for CT/NG infection internationally.

It is anticipated that one of the main challenges for TTANGO will be to sustain the involvement of health service staff amidst the numerous competing demands and health priorities, and also ensure POC operator competency is maintained in the context of high staff turnover. Regular communication and training with trial sites from a dedicated TTANGO coordinator should help to mitigate this risk. Another challenge will be if the services randomised to the POC arm in the first year prefer to keep the POC machines due to realized improvements in STI management. In the consultation phase we emphasized to health services the importance of the cross-over design to ensure long term policy change and funding. Finally, repeat positivity rates are calculated from those who re-tested and these need to be similar in both POC and non-POC arms to minimize biases – lower re-testing rates are often associated with higher repeat positivity due to re-testing in those with symptoms [53]. To mimimise any imbalance in re-testing rates, a quality improvement program and incentives associated with re-testing have been provided in both arms.

This research is significant as study outcomes will make an important contribution to the international understanding of STI control using POC tests. The research may also lead to significant decreases in STI prevalence and reinfection across multiple sites with long term benefit for the sexual health and wellbeing of young Aboriginal people. Finally, it has the potential to influence public health policy and result in [54] uptake of CT and NG POC tests into further remote clinical services in Australia, and other settings.

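### The service-level average ignores year and sequence: at six per sequence it is unbiased but can lose precision, and if sequences become unequal it carries part of any year-to-year change

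*Protocol article*

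**What the plan says.** The Statistical analysis section of the protocol article defines the primary endpoint at service level: "The primary endpoint of the study will be the health service specific difference between the two years in repeat positivity rates at three months". Treatment within seven days, the secondary endpoint, is defined the same way. For both, "the average difference between the two years (with and without POC tests) will be calculated across participating health services". No year, period or sequence term is named, and no test or standard error.

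The Study design section plans equal sequences: "In the first year, six of the health services will be randomly assigned to manage these infections under current diagnostic guidelines", and the other six start with POC testing. The Randomisation section allocates 1:1 within four regions, whose sizes are not given.

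Three further places bear on the point:

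- STI quality improvement, which applies in both phases: "health services will be supported to increase and appropriately target opportunistic STI testing, provide treatment promptly where indicated". The Clinical performance incentives section adds payments per re-test, also in both phases.
- Sample size: "At least ten services will provide data in both the intervention and control arms", out of twelve enrolled.
- Discussion: "Another challenge will be if the services randomised to the POC arm in the first year prefer to keep the POC machines".

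**The concern.** In a two-period crossover, a service's POC-minus-standard difference contains the POC effect and also whatever changed between the two years. For a service that starts with standard practice the year change enters with a plus sign; for one that starts with POC it enters with a minus sign. The randomised order is what allows the two to be separated, and the stated estimator does not use it.

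The crossover does remove stable differences between services, as the Study design section says. It does not remove a change common to all services from one year to the next. Such a change is plausible here because a programme meant to alter testing, treatment and re-testing runs throughout. The Discussion also notes that lower re-testing often goes with higher repeat positivity. That remark is about imbalance between arms, but the same mechanism could act between years.

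Two things are at stake: precision if the sequences stay equal, and bias if they do not.

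**Working it through.** **Inputs from the article (Sample size, Study design).** Repeat positivity 30% versus 15%, with a second scenario of 20% versus 10%; 150 patients tested per service-year; prevalence 15%; coefficient of variation 0.25 or 0.30; 12 services, six per sequence; at least ten with data in both years. Positives per service-year: 150 × 0.15 = 22.5.

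**Assumed, not in the article.** Two-sided alpha 0.05; normal service-level differences; a service's two years independent given the coefficient of variation; a year change g of 0, 5 or 10 points.

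**SD of a service difference, CV 0.25.** V = p0(1−p0)/n + p1(1−p1)/n + k²(p0² + p1²).

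- 30% versus 15%: 0.21/22.5 + 0.1275/22.5 + 0.0625 × (0.09 + 0.0225) = 0.00933 + 0.00567 + 0.00703 = 0.0220, so s = 0.148.
- 20% versus 10%: 0.16/22.5 + 0.09/22.5 + 0.0625 × (0.04 + 0.01) = 0.0142, so s = 0.119.

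**The plan's own power.** With ten services and a normal approximation, √(10 × 0.15²/0.0220) − 1.96 = 1.24, which gives 89.2% against the stated 88%. For 20% versus 10% the same formula gives 75.5% against the stated 78% (76.2% if n is rounded up to 23). The SD is therefore close to what the plan implies.

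**Model.** d = τ + g + e for standard-first services and d = τ − g + e for POC-first services. With N1 and N2 services in the two sequences and N in total:

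- Bias of the plain average = g(N1 − N2)/N.
- Expected variance of the differences about their plain mean = s² + 4f(1 − f)g²N/(N − 1), where f = N1/N.
- The adjusted estimate is the mean of the two sequence means. Its standard error is (s/2)√(1/N1 + 1/N2), with s pooled within sequence, on N − 2 degrees of freedom. Its bias is 0 for any split.

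**Equal sequences, 6:6.** At g = 5 points the variance is 0.0220 + 0.0025 × 12/11 = 0.0248, SD 0.157. At g = 10 points it is 0.0220 + 0.01 × 12/11 = 0.0329, SD 0.181. Simulation with t tests, 30% versus 15%:

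| Year change g | Power, plain average | Power, adjusted | Mean 95% CI width, plain (adjusted 18.6) | Type I error, plain |
|---|---|---|---|---|
| 0 | 89% | 88% | 18.4 points | 5% |
| 5 points | 86% | 88% | 19.5 points | 4% |
| 10 points | 78% | 88% | 22.6 points | 2% |

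For 20% versus 10% the plain average gives about 75%, 69% and 52%, against 74 to 75% adjusted.

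These figures are for twelve services with a t reference, so they are not a restatement of the article's 88%, which is for ten.

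**Unequal sequences.** At 6:4 the bias is g × 2/10: 1 point for g = 5 and 2 points for g = 10. At 7:5 it is g × 2/12: 0.8 and 1.7 points. If the services lost are POC-first and repeat positivity falls over time, the shift favours POC.

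**Cost of adjusting.** With no year change, power for 30% versus 15% falls by about 1 point at 6:6 (88.9% to 88.2%) and by about 3 points at 6:4 (81.5% to 78.5%). At 6:4 with g in the direction that favours POC, plain versus adjusted power is about 83% versus 78% for 5 points, part of the difference being the bias itself, and about 79% versus 78% for 10 points.

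**The case against.** The strongest reply is that the article gives only one sentence on the estimator, and that a period term and the form of the standard error are details commonly left to an analysis plan. That holds for the standard error. The power, interval-width and type I error figures depend on taking it from the spread of the differences, which the article does not say. It does not hold for the estimator, which the article states. Adding a year term would change that estimator whenever the sequences are unequal. The bias result needs no assumption about the standard error.

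Second, at the planned 6:6 the plain average and the crossover estimate are the same number. This stands. A reader might infer that the planned analysis is biased as designed, or that it makes a false claim of benefit more likely. The documents support neither: at 6:6 the estimate is unbiased and the test errs on the cautious side.

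Third, no size is given for the year change. This also stands. A reader might press a 15-point change, which would cut power to about 62%. That equals the whole target effect, and nothing in the article supports it. At 5 points the loss in the main scenario is only about 2 points of power.

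Fourth, losing two services could equally leave 5:5, with no bias, and the Discussion says that the importance of crossing over was stressed to services. That limits how likely unequal loss is. It does not remove it, because the risk the article foresees falls on one sequence only.

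**Conclusion.** The point holds in a limited form. The stated estimator ignores the randomised order. With equal sequences the consequence is precision only: about 2 points of power for a 5-point year change and about 11 for a 10-point change in the 30% versus 15% scenario, and more in the 20% versus 10% scenario. With unequal sequences the estimate is shifted by g(N1 − N2)/N, which is 1 to 2 points at 6:4 for those changes, against a 15-point target.

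This rests on assumed year changes, on a standard error formed from the service differences (for the precision figures only), and on an SD that treats a service's two years as independent. If the two years are positively correlated, the true SD is smaller and the year change is a larger share of it. The seven-day endpoint is exposed by the same reasoning, and prompt treatment is itself a target of the quality improvement programme, but the effect there has not been quantified.

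**What to change.** In the Statistical analysis section, replace the simple average with the crossover estimate: the mean of the two sequence-specific mean differences. Equivalently, add a year term to the service-level model. Take the standard error from the pooled within-sequence spread, with t on the number of services minus 2 degrees of freedom. Apply the same to the seven-day treatment endpoint.

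This takes one sentence and needs no new data, since sequence is already randomised. The price is one degree of freedom and, when sequences are unequal, a somewhat less efficient weighting; the power cost with no year change is given in the working.

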## Discussion

Rates of CT and NG in remote Aboriginal communities in Australia are unacceptably high, and TTANGO will evaluate whether POC testing for these STIs can improve the timeliness of treatment and in turn reduce repeat infection rates. To our knowledge, TTANGO will be the first randomized trial of molecular POC tests for CT/NG infection internationally.

It is anticipated that one of the main challenges for TTANGO will be to sustain the involvement of health service staff amidst the numerous competing demands and health priorities, and also ensure POC operator competency is maintained in the context of high staff turnover. Regular communication and training with trial sites from a dedicated TTANGO coordinator should help to mitigate this risk. Another challenge will be if the services randomised to the POC arm in the first year prefer to keep the POC machines due to realized improvements in STI management. In the consultation phase we emphasized to health services the importance of the cross-over design to ensure long term policy change and funding. Finally, repeat positivity rates are calculated from those who re-tested and these need to be similar in both POC and non-POC arms to minimize biases – lower re-testing rates are often associated with higher repeat positivity due to re-testing in those with symptoms [53]. To mimimise any imbalance in re-testing rates, a quality improvement program and incentives associated with re-testing have been provided in both arms.

This research is significant as study outcomes will make an important contribution to the international understanding of STI control using POC tests. The research may also lead to significant decreases in STI prevalence and reinfection across multiple sites with long term benefit for the sexual health and wellbeing of young Aboriginal people. Finally, it has the potential to influence public health policy and result in [54] uptake of CT and NG POC tests into further remote clinical services in Australia, and other settings.
